## 7.2 Definition and Reporting of a Serious Adverse Event

### 7.2.1 Definition of a Serious AE

A serious AE is any untoward medical occurrence that at any dose (based on ICH and EU Guidelines on Pharmacovigilance for Medicinal Products for Human Use):

- Results in death
- Is life-threatening (defined as an event in which the subject or patient was at risk of death at the time of the event; it does not refer to an event which hypothetically might have caused death if it were more severe)

- Requires inpatient hospitalization or causes prolongation of existing hospitalization
- Results in persistent or significant disability/incapacity
- Is a congenital anomaly/birth defect

Medical and scientific judgment should be exercised in deciding whether expedited reporting is also appropriate in situations other than those listed above. For example, important medical events may not be immediately life-threatening or result in death or hospitalization but may jeopardize the subject or may require intervention to prevent one of the outcomes listed in the definition above (e.g., suspected transmission of an infectious agent by a medicinal product is considered a serious adverse event). Any adverse event is considered a serious adverse event if it is associated with clinical signs or symptoms judged by the investigator to have a significant clinical impact.

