| Study phase:                                           | IV                                                                                                                                                                                                                                                                                                                                                                                                                                                                                                                                                                                                                                                                                                                                                |
| Study design:                                          | Randomized, controlled, open-label multicenter study                                                                                                                                                                                                                                                                                                                                                                                                                                                                                                                                                                                                                                                                                              |
| Indication:                                            | Ankylosing spondylitis (AS)                                                                                                                                                                                                                                                                                                                                                                                                                                                                                                                                                                                                                                                                                                                       |

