|                 | 
n=190; assuming a 10% screening failure rate approximately.
 
To be allocated to trial:
n=170 patients with active AS despite treatment with NSAIDs alone will be included in the phase I of the trial and treated with Golimumab. Only patients with good clinical response after 12 weeks of treatment will be enrolled in the phase II of the trial. It is assumed that approximately 60% (n=100) of patients included in phase I will continue in the phase II of the study, considering that elevated CRP at baseline is currently the best response predictor for TNF-blocker therapy.
 
To be analysed:
n=100 (n=50 in each group) patients will enter phase II of the trial (intention-to-treat population - ITT) after 1:1 randomization.
 
Statistical analysis:
 
Efficacy:
Efficacy of the therapy in reduction of radiographic spinal progression will be assessed by the modified Stoke Ankylosing Spondylitis Spine Score (mSASSS). mSASSS is a radiographic score measuring structural changes in the lumbar and cervical spine. Images will be scored by 2 trained readers in a blinded manner that allows the open-label (although randomized) design of the trial.
The primary efficacy endpoint will be radiographic spinal progression assessed by the change in the mSASSS score over two years of therapy in both groups. The primary analysis will be based on the intention-to-treat population, a secondary one in patients with complete sets of radiographs at two time points. A two-sided Mann-Whitney U-test will be applied to compare the mSASSS progression between both treatment groups in both analyses.
 
Safety:
Safety outcome will include absolute number and percentage of patients who experienced adverse events (AE), serious AE, AE of interest (infections, malignancies, gastrointestinal events: ulceration, bleeding, perforation, gastric outlet obstruction; thrombotic cardiovascular events: myocardial infarction, stroke, pulmonary artery embolism, peripheral arterial of venous thrombosis; renal and hepatic function deterioration), as well as a proportion of patients who discontinued the study because of AEs.
In order to address possible long-term safety issues related to long term use of NSAIDs a safety Follow-Up Visit will be performed 3 months after discontinuation of the study treatment (either week 108 or the last study visit in the case of early discontinuation).
Safety population will include each patient who received at least one dose of Golimumab with or without Celecoxib. Statistical comparisons will be based on event rates per 100 patient years of exposure. Rates will be compared by exact Poisson methods.
 
Secondary endpoint(s):
Mann-Whitney U-test, linear mixed models, and Chi-square test will be used in order to evaluate differences in the secondary outcome parameters between treatment groups.
 |

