All identified AEs must be recorded and described on the appropriate AE section of the CRF. If known, the diagnosis of the underlying illness or disorder should be recorded, instead of the individual symptoms. The following information should be captured for all AEs: date of onset and resolution, severity of the event (see definitions), investigator's opinion of the relationship to investigational product (see definitions), treatment required for the AE, cause of the event (if known), and information regarding resolution/outcome. The following categories and definitions of severity should be used:

- Mild (Grade I) - awareness of event but easily tolerated.
- Moderate (Grade II) - discomfort enough to cause some interference with usual activity.
- Severe (Grade III) - inability to carry out usual activity.
- Very severe (Grade IV) - debilitating significantly incapacitates subject despite symptomatic therapy.

The following categories and definitions of causal relationship to study drug should be used:

- No related: there is no causal relationship (in the opinion of the investigator) between the AE and use of the study drug.
- Doubtful: there are other factors such as concomitant disease, medications or the relationship in time, suggesting that a causal relationship is unlikely.
- Possible: the AE might be due to the use of the drug. Other factors such as concomitant drug or disease are inconclusive. The relationship in time is reasonable; therefor, the causal relationship cannot be excluded.
- Probable: there is a reasonable causal and temporal relationship between the study drug and the AE. Other reasons are less likely.
- Very likely: there is a reasonable causal and temporal relationship between the study drug and the AE. The AE is described as a side effect of the study drug and cannot be reasonably explained by an alternative explanation. The relationship in time is very suggestive (e.g. it is confirmed by dechallenge and rechallenge).

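### The last sentence of the serious-AE definition (section 7.2.1) lets an investigator who knows the arm add events to the SAE count with no stated threshold, alongside the bounded criteria

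*Protocol*

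**What the plan says.** Section 7.2.1 of the protocol offers three routes to the label serious.

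1. It opens with "A serious AE is any untoward medical occurrence that at any dose" and lists five outcomes: death, threat to life, hospitalisation or its prolongation, lasting or significant disability, and congenital anomaly. The list is said to follow ICH and EU guidance.
2. It adds medical judgement for important events that "may jeopardize the subject or may require intervention to prevent one of the outcomes listed in the definition above".
3. It closes by saying that any AE is "considered a serious adverse event if it is associated with clinical signs or symptoms judged by the investigator to have a significant clinical impact".

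Severity is recorded separately under section 7.1. Grade II is "discomfort enough to cause some interference with usual activity", and the next grade reads "Severe (Grade III) - inability to carry out usual activity".

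The synopsis calls the trial a "Randomized, controlled, open-label multicenter study". Blinding is described only for the readers of the spinal radiographs (synopsis; section 13.7). Serious AEs are a named safety outcome (synopsis; section 5.2). The synopsis plans statistical comparison of safety events as rates per 100 patient-years: "Rates will be compared by exact Poisson methods". Section 13.6 says only that serious AEs will be summarised separately.

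**The concern.** The first two routes are bounded, by an outcome in one case and by jeopardy or prevention of an outcome in the other. The third keeps the judgement and drops the bound. Two investigators could classify the same event differently, with no hospital stay and no jeopardy, and both would be following the protocol. The phrase also describes how hard the event hits the patient, which is what the severity grades already record, so severity and seriousness become mixed.

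Because treatment is open-label, the person making this call knows the arm. If investigators use the third route more readily in one arm, the SAE rates will differ without any difference in criterion-based events. Section 4.3.3 says a radiographic benefit would have to be weighed against the risks of continuous NSAID use, so the safety contrast matters to the trial's conclusion. Each event labelled serious by this route also falls under the 24-hour reporting rule and reaches the DSMC as an SAE.

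**Working it through.** **Text check: does anything elsewhere narrow the sentence?**

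- Section 7.2.2 sets minimum content for the SAE form. The list includes event description, relationship and outcome, but not the seriousness criterion met. Unless the form goes beyond this minimum, events admitted only by the third route are not directly identifiable at analysis.
- Section 14 has the principal investigator review SAEs to decide SUSAR status. It does not describe blinded review of seriousness.
- Section 7.4 has the DSMC review SAEs as reported.
- Section 13.7 limits blinding to the radiographs.

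Nothing narrows it.

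**Illustration of size.** The protocol gives no SAE rate, so there is no figure of its own to reproduce.

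Inputs from the protocol: 50 patients per arm (synopsis) and 96 weeks of randomised treatment (section 13).

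Exposure per arm, ignoring dropout = 50 × 96 / 52.18 = 92.0 patient-years.

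Assumed inputs, none of them in the documents:
- r = criterion-based SAEs per 100 patient-years, equal in both arms: 4, 6 or 8. Expected events per arm are 0.92 × 4 = 3.7 to 0.92 × 8 = 7.4.
- e = extra SAEs per 100 patient-years admitted only by the third route in one arm: 5 or 10.
- k = relative frequency of such calls in the other arm: 1.25 or 1.5.

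Apparent rate ratio = (r + e·k) / (r + e). The true ratio on criterion-based events is 1.0. Rejection is the probability that a two-sided exact conditional (binomial) test of two Poisson rates gives p ≤ 0.05.

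| r | e | k | Apparent ratio | Rejection |
|---|---|---|---|---|
| 4 | 5 | 1.25 | 10.25/9 = 1.14 | 3.5% |
| 4 | 5 | 1.5 | 11.5/9 = 1.28 | 5.2% |
| 4 | 10 | 1.25 | 16.5/14 = 1.18 | 4.6% |
| 4 | 10 | 1.5 | 19/14 = 1.36 | 9.4% |
| 6 | 5 | 1.25 | 12.25/11 = 1.11 | 3.4% |
| 6 | 5 | 1.5 | 13.5/11 = 1.23 | 4.9% |
| 6 | 10 | 1.25 | 18.5/16 = 1.16 | 4.6% |
| 6 | 10 | 1.5 | 21/16 = 1.31 | 8.9% |
| 8 | 5 | 1.25 | 14.25/13 = 1.10 | 3.4% |
| 8 | 5 | 1.5 | 15.5/13 = 1.19 | 4.7% |
| 8 | 10 | 1.25 | 20.5/18 = 1.14 | 4.6% |
| 8 | 10 | 1.5 | 23/18 = 1.28 | 8.6% |

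For reference, when the extra calls are equal in both arms (k = 1) the exact test rejects about 3% of the time. The risk therefore comes from unequal use of the sentence, not from the sentence adding events as such.

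**The case against.** The strongest reply is that the sentence closes a paragraph about medical judgement and can be read as part of the important-medical-event clause. It leans towards over-reporting, which is the safe direction for patient protection. The risks most associated with celecoxib are captured elsewhere: section 5.2 lists gastrointestinal and thrombotic cardiovascular events of interest and gives numeric renal and hepatic limits, and none of these depends on the SAE label. Severity is tabulated in its own right under section 13.6. The Poisson comparison appears only in the synopsis. Discharge letters and event descriptions would probably allow many criterion-based events to be identified afterwards.

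Most of this stands, and it limits the point without removing it. The sentence as written covers any AE and does not repeat the jeopardy condition, so the narrower reading has to be supplied by the reader.

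Four stronger readings are tempting but unsupported.

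- A reader might infer that the SAE rate rests on the subjective sentence instead of the listed outcomes. It rests on the sentence in addition to them.
- A reader might infer that Grade II events, such as dyspepsia or a minor infection, become serious. The protocol does not equate some interference with usual activity with significant clinical impact; an investigator would have to judge the impact significant in each case.
- A reader might infer a bias against celecoxib. The documents fix no direction.
- A reader might infer a large false-positive risk. With criterion-based rates of 5 or 10 per 100 patient-years, rejection reaches 16.1% or 11.1% if 5 extra events fall in one arm only, and 50.2% or 34.2% if 10 do. Those cases need every extra call to fall in a single arm, far beyond a 25-50% difference.

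**Conclusion.** The point holds as a limited defect in the safety definition. Section 7.2.1 contains an unbounded, arm-aware route into the SAE count beside two bounded ones, and nothing else in the protocol closes it.

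Neither the size nor the direction of any bias can be derived from the documents. Over the assumed grid the apparent ratio is 1.10-1.36 when the true ratio is 1.0, and exact-test rejection is 3.4-9.4% against about 3% with equal use. The likelier harm is a blurred point estimate, not a false significant result. The figures assume 50 patients per arm with full 96-week exposure.

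The mSASSS endpoint and the events of interest are untouched. The change is worth making mainly because it costs so little.

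**What to change.** 1. In section 7.2.1, tie the closing sentence to the important-medical-event wording before it, so that it applies only where the event may endanger the subject or needs intervention to avert a listed outcome. Alternatively, delete it.
2. Add to the SAE form a field for the seriousness criterion met.
3. Base the between-arm SAE comparison on events meeting a listed criterion or the important-medical-event clause.
4. Keep sending other events of clinical concern to the DSMC as AEs, so that no safety information is lost.

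The cost is one amended sentence, one form field and one line on the analysis. The downside is that slightly fewer events carry the serious label. Some judgement by unblinded investigators remains through the important-medical-event clause, but it is bounded and, with the new field, visible at analysis.

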### 7.2.2 Reporting a Serious AE

All serious AEs (SAE) whether related or unrelated to investigational product, must be reported to the sponsor within 24 hours of being made aware of the serious AE:

Med. Klinik I, Rheumatologie  
Campus Benjamin Franklin  
Charité Universitätsmedizin Berlin  
[name]  
[name]  
[contact]  
**[contact]**

The SAE report form should include at least the following information: study title, study centre identifier, patient number, age, sex, height and weight of the patient, date of the event onset, description of the event, concomitant diseases and medications, action taken, evaluation of the relationship with the study drug or study procedure, outcome. The first report should contain at least the following information: study title, study drug, study centre identifier, patient number, SAE description and investigator's statement on relationship to the study drug.

Collection of complete information concerning SAEs is highly important. Therefore, follow-up information which becomes available as the SAE evolves, as well as supporting documentation (e.g., hospital discharge letter, autopsy reports), should be notified to the

sponsor subsequently, if not available at the time of the initial report, and sent within 24 hours of being made aware using the same procedure as the initial SAE report.

All SAEs must be collected within the entire study period (108 weeks treatment and 4 weeks of follow-up) or at least 30 days after the last drug administration if the patient discontinues the study prematurely. In addition, any SAE occurring after this time period, which might be, in the opinion of the investigator, very likely, probably or possibly related to investigational product, will be reported.

The sponsor / principal investigator will be responsible for submitting of “Suspected Unexpected Serious Adverse Reaction (SUSAR)” reports to the Independent Ethics Committee and to regulatory authority and for writing and submitting the “Annual Safety Report” concerning safety of the included subjects.

### 7.3 Pregnancy

All female subjects of child-bearing age require a negative pregnancy test at trial entry. Female patients are required to use an adequate contraception method throughout the study period and at least 6 months after the last Golimumab injection (as outlined in chapter 6.3.1 “Inclusion Criteria”, paragraph 8). If any subject becomes pregnant during the study, she will be immediately withdrawn from the trial. In the case of pregnancy this must be reported on AE pages although the pregnancy per se is not considered an AE. However, the medical outcome of an elective or spontaneous abortion, stillbirth or congenital anomaly will be considered a serious AE and must be reported immediately (within 24 hours of the site becoming aware of the event). Follow-up information regarding the outcome of the pregnancy and any postnatal sequelae in the infant will be required.

### 7.4 Data and Safety Monitoring Committee (DSMC)

Safety data, especially SAE / SUSAR, but also cumulated AEs will be reviewed by an external Data and Safety Monitoring Committee consisting of 3 experienced rheumatologists otherwise not related with this clinical study. Meeting of the DSMC will take place at least once yearly.

## 8 PLANNED TREATMENT OF THE PATIENTS AFTER STUDY END

Patients will receive the standard treatment with standard care as needed throughout and after the study. After Week 108 any additional or changed treatment is left to the discretion of the investigator and the patient.

Add-on studies or additional scientific projects linked to this study are possible. Subjects having terminated study participation or still participating may participate in these studies/projects if this is not contradictory to this protocol.

## 9 OVERALL RISK/BENEFIT ASSESSMENT

### 9.1 Celecoxib

NSAIDs are the standard medical treatment in AS. Given the chance that NSAIDs may inhibit structural damage, continuous treatment with an NSAID for a period of 2 years in addition to TNF-blocker treatment might therefore contribute to the improvement of the long-term outcome besides just symptomatic improvement, especially in subjects at risk (i.e. presence of elevated CRP and syndesmophytes). NSAIDs treatment might be particularly beneficial in patients with these characteristics as several studies indicated. Possible risks of NSAIDs in the treatment of rheumatic diseases as AS are well described and patients with AS are at lower risk for side effects of NSAIDs including Celecoxib because of lower age and lower prevalence of comorbidities in comparison to other rheumatic conditions such as rheumatoid arthritis or osteoarthritis. Generally COX-2 selective NSAIDs have a lower risk of producing severe gastrointestinal side effects than non-selective NSAIDs. Nevertheless, since the combined treatment group will be taking daily Celecoxib for 2 years, a concomitant therapy with PPI can be prescribed to reduce the risk of gastrointestinal AE (decision of the investigator).

High risk patients for experiencing cardiovascular side effects will be excluded from this study. The high risk is defined as having > 2 risk factors (e.g., uncontrolled hypercholesterolemia, diabetes mellitus, smoking, uncontrolled arterial hypertension). Medical history of myocardial infarction, recent angina pectoris, significant heart insufficiency (NYHA II or IV) as well as diagnoses of coronary heart disease and peripheral arterial occlusive disease are exclusion criteria.

Because of younger age and less comorbidities of AS patients as compared to those with rheumatoid arthritis or osteoarthritis in most of the clinical trials, we expect a low number of serious adverse cardiovascular events. Two recent observational studies demonstrated that NSAIDs intake including Coxibs in AS patients is associated with no excess (or even lower) in cardiovascular risk as compared to the general population.

### 9.2 Golimumab

For those patients with AS and unsatisfactory response to previous NSAIDs, TNF blocking therapy (including Golimumab) is the second line therapy currently available, along with recently approved secukinumab in EU. Up to date, between 250-300.000 patients were treated with Simponi® world-wide (personal information by MSD Sharp & Dohme, spring 2016).

The major potential risks of Golimumab treatment are infections, development of malignancies and hypersensitivity reactions. Recently an analysis of pooled data from the long-term extension clinical trials (up to 3 years) with patients with RA, PsA or AS receiving Golimumab has been published. Across five phase-III studies with Golimumab SC, 639 patients received placebo and 2,226 were treated with Golimumab for up to 3 years (1,249 patients were treated with Golimumab 50mg SC and 1,501 patients with Golimumab 100mg SC); a total of 1,179 subjects received Golimumab for over 156 weeks. The collected results indicate that in general Golimumab safety profile is similar to the known safety profile of other TNF  $\alpha$  blockers.

Hypersensitivity reactions in clinical studies of Golimumab, rash and urticarial, have each been observed in < 2% of patients.

Formation of antibodies against TNF  $\alpha$  agents has been related in different studies to a possible cause of the development of resistance or gradual drug failure and to a risk of development of hypersensitivity reaction. The risk of producing antibodies varies with each specific type of TNF-blocker, most commonly present with infliximab and adalimumab therapy. Consistently in all studies performed with Golimumab, antibodies against Golimumab were detected in a small number of subjects without a clear influence on the response to therapy; this observation suggests that the presence of anti-Golimumab antibodies does not necessarily affect the efficacy of Golimumab.

Based on these considerations we assume a favourable risk/benefit profile of this study. In order to minimize the overall risk to participating subjects, this protocol has inclusion and exclusion criteria appropriate to the population and proposed treatments, exclusionary screening tests, and specific follow-up safety assessments.

These criteria and assessments are also orientated to established international and national practice guidelines (EULAR^8, DGRh).

